### Recruitment and allocation

2.1

Patients with pathologically and/or cytologically diagnosed GA/GEJA who underwent D2 gastrectomy were potentially eligible for enrollment, and every consenting patient signed the informed consent form (ICF) prior to actual enrollment.

The criteria for eligible patients included 18- to 75-year-old males and females (female participants should not be pregnant or lactating), patients histologically or cytologically diagnosed with stage III GA/GEJA (Siewert III), patients who underwent D2 gastrectomy and achieved R0 or R1 resection, patients with an Eastern Cooperative Oncology Group (ECOG) performance status between 0 to 1, and patients without significant defects in organ function. Considering that the detection of ctDNA via next-generation sequencing (NGS) may take up to 10 working days, patients who received only the first cycle of XELOX chemotherapy will also be accepted for enrollment. The major exclusion criteria included serious/uncontrollable hypertension/cardiac insufficiency/infection/diabetes/renal insufficiency, tendency for gastrointestinal hemorrhage, immune deficiency, recent thrombotic event or any other situation deemed unsuitable for enrollment by the researcher. A more detailed version of our inclusion/exclusion criteria is provided in **Supplementary Materials**.

The recruited patients will be subjected to ctDNA analysis (Geneseeq Technology Co., Ltd., Nanjing, China; 1021 genes NGS) 3-8 weeks after the operation. Patients with positive ctDNA will be randomly allocated to two arms (arms A&B). Patients with negative ctDNA will constitute arm C. Patients who are ctDNA positive but for various reasons fail in random allocation will be assigned to arm D.

Block randomization is used in this study, with a block size of 4. Random allocation sequence including randomization seed, block size and block counts are provided by our statistics specialist. A central randomization is established, in which researchers will enter the participants’ general information, including abbreviation of participant’s name, gender and age to apply for a randomization number and allocation into arms. This randomization number will be included in the participant’s medical history, and the participant will receive treatment according to the allocated arm.

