### Statistical analysis

2.6

Previous research reported that the median DFS of postoperative adjuvant chemotherapy in ctDNA-positive GA/GEJA patients is approximately 12 months (13, 14). Our hypothesis is that anlotinib plus penpulimab combined with XELOX will prolong DFS to 24 months. Setting the single-sided α as 0.05, β as 0.2, the length of in-group time as 18 months and the length of follow-up as 24 months, the calculated sample size is 36 patients for the test group (arm A) and 36 patients for the control group (arm B); presuming that the drop-off rate is 10%, the total number of participants needed is 40 each group. The key secondary endpoint is the difference in DFS between ctDNA-positive and ctDNA-negative patients treated by only chemotherapy. Given that the median DFS of ctDNA-negative patients receiving standard treatment is approximately 36 months, two-sided α = 0.05, β = 0.2, the length of in-group time is 18 months, and the length of follow-up is 36 months, the sample size should be 14 each for the ctDNA-positive group and the ctDNA-negative group. Taking both hypotheses into consideration, we presume at least 80 ctDNA-positive patients would be needed to complete this study. Considering that the positive rate of ctDNA in postoperative GA/GEJA patients is approximately 25-30%, a total of 300 participants needs to be screened.

Statistical analysis will be carried out by statistics specialists who will take part in the study during the whole process, from the study design and implementation to the data analysis phase. Measurement variables will be analyzed by means of *t test*, paired *t test*, rank-sum test, paired rank-sum test, analysis of variance (ANOVA), etc. Count variables will be analyzed using the Cochran–Mantel–Haenszel (CMH) chi-squared test, logistic regression and Fisher’s exact test. Ordinal variables will be analyzed via the rank-sum test. Survival data will be compared via the Kaplan–Meier method or Cox regression. The main clinical response indicators will be subjected to per-protocol population (PP) and full analysis set (FAS) analyses simultaneously. A two-sided test for significance was performed as the default, and *P<*0.05 was considered significant. The analysis will be performed using SAS software. The data analysis is planned to be at mid-term and upon completion of this trial.

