## Trial status

4

We estimate that this clinical study will last for 18 months, starting from July 2022 to February 2024. Patients will be recruited from multiple centers across Jiangsu Province. A total of 300 patients will be screened for this trial.

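### Screening 300 patients yields fewer than the required 80 at the lower end of the plan's own ctDNA-positive range, and the figure treats every positive patient as randomised (minor)

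*Protocol article*

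**What the plan says.** All of this is in the Protocol article.

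- **Section 2.6, Statistical analysis (primary comparison).** The calculation gives 36 patients per arm, and then "presuming that the drop-off rate is 10%, the total number of participants needed is 40 each group". That makes 80 randomised patients.
- **Section 2.6 (carry-over to screening).** The requirement is restated in terms of ctDNA status: "we presume at least 80 ctDNA-positive patients would be needed to complete this study". The next sentence turns it into a screening number: "Considering that the positive rate of ctDNA in postoperative GA/GEJA patients is approximately 25-30%, a total of 300 participants needs to be screened".
- **Section 2.1, Recruitment and allocation.** Not every positive patient enters the comparison: "Patients who are ctDNA positive but for various reasons fail in random allocation will be assigned to arm D". The abstract describes arm D in the same way. No expected size for arm D is given.
- **Section 4, Trial status.** The number is repeated as a total: "A total of 300 patients will be screened for this trial". The abstract also gives 300 as the total.

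**The concern.** Two steps in the chain from 40 per arm to 300 screened do not fit together.

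First, the requirement is a minimum of 80 and the positive rate is a range, but the single screening figure meets the minimum only over part of that range. At 25% it gives 75.

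Second, the unit changes. The 80 comes from 40 randomised patients in each of two arms, yet it is carried forward as a count of ctDNA-positive patients. The design itself provides for positives who are not randomised, and the screening figure leaves no room for them.

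At stake is the size of the arm A versus arm B comparison. It is planned at 80% power for a doubling of median DFS, with almost no reserve, so a shortfall in randomised patients lowers power directly.

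**Working it through.** **Inputs (section 2.6 unless noted).** Median DFS 12 versus 24 months, so HR 0.5 under exponential DFS; one-sided α 0.05; β 0.2; accrual 18 months; follow-up 24 months; drop-off 10%; ctDNA-positive rate 25-30%; 300 screened. Allocation is 1:1 (abstract). The arm D share is not given; 10% is used below purely as an illustration.

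**1. Reproducing 36 and 40 per arm.**
- Events (Schoenfeld): 4 × (1.645 + 0.842)² / (ln 0.5)² = 51.5, so 52.
- Event probability with uniform accrual over 18 months and 24 months' follow-up after accrual ends: 1 − [exp(−24λ) − exp(−42λ)] / (18λ), with λ = ln 2 / median. This gives 0.845 (control) and 0.610 (experimental), mean 0.727.
- Per arm: 52 / 0.727 / 2 = 35.7, so 36. This matches the plan.
- Drop-off: 36 / 0.9 = 40. This matches the plan, and it uses up the 10% allowance.

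**2. Reproducing 300.**
- At the midpoint of the range: 80 / 0.275 = 291, which rounds up to 300. The figure is therefore consistent with planning at about the middle of the range with every positive randomised.

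**3. The same step across the stated range, no arm D losses.**

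| Positive rate | Expected positives from 300 | Screening needed for 80 | Exact binomial chance of at least 80 positives from 300 |
|---|---|---|---|
| 25% | 75 | 320 | 27% |
| 27.5% | 82.5 | 291 | 65% |
| 30% | 90 | 267 | 91% |

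The break-even rate is 80 / 300 = 26.7%. The share of the range below it is (26.7 − 25) / (30 − 25), about one third.

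**4. Can the 10% drop-off double as an arm D allowance?** No. At 25%, 75 × 0.9 = 67.5, which is below the 2 × 36 = 72 needed before drop-off.

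**5. Power under the plan's own convention.** Here drop-offs contribute nothing, so events d = randomised × 0.9 × 0.727 and power = Φ(√d × 0.693/2 − 1.645).
- 80 randomised: d = 52.4, power 80.6%.
- 75 randomised (25% rate, no arm D): d = 49.1, power 78.3%.
- 67.5 randomised (25% rate, assumed 10% to arm D): d = 44.2, power 74.5%.

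**6. Illustration with an assumed 10% of positives in arm D.**
- Screening needed: 80 / (0.25 × 0.9) = 356 at 25%, and 80 / (0.30 × 0.9) = about 296 at 30%.
- Break-even rate: 80 / (300 × 0.9) = 29.6%.

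**The case against.** The strongest reply is that nothing has been miscalculated. The rate is approximate, the midpoint gives 291, and 300 is a sensible rounding that suffices on expectation over about two thirds of the range. That stands: the weakness is the choice of planning value and the change of unit, not a slip in division.

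A second reply is that the power effect is slight. That also stands for the 25% rate taken alone, where the loss is about 2 points. It may be smaller still. The article plans a full analysis set with Kaplan–Meier or Cox methods, in which patients who drop off count until censoring. If all 75 contributed fully, 75 × 0.727 = 54.5 events would give about 82% power.

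A third reply is that no passage says recruitment closes at 300 if fewer than 80 have been randomised, and that the 80 is worded as a minimum. A rule for continuing to screen could well be in the full protocol, which is not shown. A reader might infer a hard stop from the repeated total of 300, but the article does not state one, and the absence of a continuation rule is not counted against it here.

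What these replies do not answer is that a stated minimum of 80, a stated rate of 25-30% and a stated 300 disagree at the lower end of the range, and that 80 positives are treated as 80 randomised in a design that has an arm for positives who are not randomised.

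**Conclusion.** The point holds in a limited form and is minor. Screening 300 delivers an expected 75 to 90 positives, falls short of 80 below a rate of 26.7%, and carries no allowance for arm D. On the document's own figures the cost is a fall in power from about 81% to about 78% at the 25% rate. This assumes exponential DFS, HR 0.5, one-sided 0.05, 24 months' follow-up after accrual, and 10% of patients contributing no information.

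A reader might go further and conclude that the trial will be undersized over most of its range, or that its power is really 75% or lower. The document does not support this. Those results need an arm D share, and none is given; the 74.5% above shows only what a 10% share would do. Nor does the document show that the trial would stop at 300 regardless of how many patients had been randomised.

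**What to change.** In section 2.6, state the recruitment target as 80 randomised patients (40 per arm), not 80 ctDNA-positive patients. Describe 300 as an estimate and not a stopping point, and restate it as about 267 to 320 screened before arm D losses. If an arm D share is expected, state it and adjust; at an assumed 10% the range is about 296 to 356. Bring the abstract and section 4 into line.

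These are expected-value figures. At a 25% rate, about 360 would have to be screened for a 90% chance of at least 80 positives even with no arm D losses, so a target defined by randomised patients protects the comparison better than any fixed screening number.

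If 300 is meant as a cap, keep it and state that 75 randomised patients give about 78% power at the 25% rate, and less with arm D losses.

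The cost is a few changed sentences, plus either some extra ctDNA tests if the lower rate occurs or a slightly lower stated power.

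### Two analysis times and two populations share one P<0.05 default, and the article does not say which analysis decides DFS for arm A versus arm B

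*Protocol article*

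**What the plan says.** All the relevant statements are in section 2.6, Statistical analysis, of the protocol article.

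- **Timing:** "The data analysis is planned to be at mid-term and upon completion of this trial". No endpoint, information fraction, boundary or purpose is given for the mid-term analysis.
- **Populations:** "The main clinical response indicators will be subjected to per-protocol population (PP) and full analysis set (FAS) analyses simultaneously". No order between the two is given.
- **Threshold:** "A two-sided test for significance was performed as the default", and a P value below "0.05 was considered significant".
- **Design of the primary comparison:** "Setting the single-sided α as 0.05, β as 0.2", with 36 patients per arm, raised to 40 for a 10% drop-off.

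Section 2.2 makes DFS of arm A versus arm B the primary endpoint and describes the trial as open-label.

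**The concern.** The three statements on timing, populations and threshold stand next to each other, and nothing ranks or separates them. DFS is the primary endpoint, so it is natural to count it among the main indicators. Applied literally, the plan then allows four tests of A versus B: two times by two populations, each at 0.05. The sample size was derived for one.

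Two things are at stake. The first is the type I error of the primary claim. The second holds even if the mid-term analysis never touches efficacy. PP removes patients for reasons that arise after randomisation. In this open-label trial those reasons can differ by arm: section 2.4 places the anlotinib dose-modification rules and the penpulimab discontinuation rule on arm A only, and section 2.2 gives maintenance treatment to arm A only. With 40 patients per arm, a few unequal exclusions could move the result.

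**Working it through.** **1. Reproduce the plan's sample size.** Inputs from section 2.6: "the median DFS of postoperative adjuvant chemotherapy in ctDNA-positive GA/GEJA patients is approximately 12 months"; "anlotinib plus penpulimab combined with XELOX will prolong DFS to 24 months"; "the length of in-group time as 18 months and the length of follow-up as 24 months"; one-sided 0.05 and 80% power. Exponential survival and uniform accrual are assumed.

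- Hazard ratio = 12/24 = 0.5.
- Events (Schoenfeld) = 4(1.645 + 0.842)² / (ln 0.5)² = 51.5, so 52.
- Event probability = 1 − [exp(−24λ) − exp(−42λ)] / (18λ), with λ = ln 2 / median. Arm B: 0.845. Arm A: 0.610.
- Patients per arm = 52 / (0.845 + 0.610) = 35.7, so 36. Then 36/0.9 = 40.

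The stated 36 and 40 reproduce with a single final test and no allowance for an earlier one.

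**2. Two looks, one population, each at 0.05.** Under the null hypothesis the test statistics at the two looks are bivariate normal with correlation √t, where t is the information fraction at mid-term. The article gives no t, so a range is shown.

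| t (assumed) | one-sided 0.05 | two-sided 0.05 |
|---|---|---|
| 0.3 | 8.6% | 8.9% |
| 0.5 | 8.0% | 8.3% |
| 0.7 | 7.3% | 7.6% |

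**3. Two looks by two populations, any success counts.** If a fraction e is excluded from PP at random, the correlation between the PP and FAS statistics is √(1 − e): 0.949 for e = 10% and 0.894 for e = 20%. Both fractions are assumptions; the 10% drop-off in section 2.6 is not a PP exclusion rate. Simulation at t = 0.5 (4 million draws) gives:

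| e (assumed) | one-sided 0.05 | two-sided 0.05 |
|---|---|---|
| 10% | about 10% | 10.6% |
| 20% | 10.8% | 11.6% |

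For t from 0.3 to 0.7 and correlations from 0.8 to 1.0, the two-sided figure runs from about 7.6% to 13.7%. A choice between PP and FAS at the final analysis only gives 6.3% (one-sided, 10% excluded) to 7.1% (two-sided, 20% excluded).

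**4. Count only false claims in favour of arm A under the two-sided default.** A single test carries 2.5% in that direction. Two looks at t = 0.5 in one population give 4.2%. All four tests give 5.3% (10% excluded) to 5.8% (20% excluded).

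**5. Boundaries that restore 5%**, with FAS the only decisive set and t = 0.5 (O'Brien-Fleming):

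- One-sided 0.05: z = 2.373 then 1.678, that is P<0.0088 then P<0.0467.
- Two-sided 0.05: z = 2.797 then 1.977, that is P<0.0052 then P<0.0480.

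**The case against.** A reader might infer that the plan's false-positive rate simply is 8-11% instead of 5%. The document does not support that. The mid-term sentence names no endpoint and no option to claim success. The population sentence does not say that either set is enough. The threshold is offered as a general default. If significance were required in both sets at the same look, two looks would give only about 5.1% to 6.0% (correlations 0.90 and 0.95, two-sided). If the mid-term analysis does not test DFS and FAS decides, the error is 5%. This part of the objection stands, and every figure above is conditional.

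It is also fair that section 2.6 uses two different 5% levels, one-sided for the design and two-sided as the default. Under the two-sided default, false claims for arm A reach only 4.2% to 5.8%, close to the one-sided 5% of the design. That is still about 1.7 to 2.3 times the 2.5% of a single two-sided test (4.2/2.5 and 5.8/2.5).

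Finally, interim boundaries and the choice of primary set are often left to a full protocol or SAP, and this is a condensed article. Silence alone would therefore be no finding. But the article is not silent. It fixes the number of analyses, puts two populations on an equal footing and sets one threshold, and that combination works badly if it is followed as written. Reporting both FAS and PP is ordinary practice; the difficulty is only that neither is said to decide.

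The random-exclusion model in step 3 describes multiplicity only. It does not measure the bias from exclusions that differ by arm, and the documents give nothing from which to estimate that bias.

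**Conclusion.** The concern holds in conditional form. As worded, section 2.6 does not secure the stated alpha for A versus B, because it leaves open which of up to four analyses decides. With DFS tested at both times in one population, the error is about 8.0% (one-sided) or 8.3% (two-sided) at an assumed 50% information, and 7.3% to 8.9% over 30-70% information. With any of four tests counting, it is about 10% to 11.6% at 50% information and 10-20% random PP exclusions. None of these conditions is stated in the article. Independently of the arithmetic, a positive claim resting on PP alone would not be a randomised comparison. For a phase II trial whose decision rule is unstated and easily clarified, this is a should-fix point.

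**What to change.** Add two statements to section 2.6, before any comparative results are seen.

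(a) The mid-term analysis covers safety and trial conduct only and makes no efficacy test of arm A against arm B. If an efficacy test is wanted, use an O'Brien-Fleming boundary on the same sidedness as the primary test. At 50% information this is P<0.0088 then P<0.0467 for one-sided 0.05, or P<0.0052 then P<0.0480 for two-sided 0.05. Recompute the limits if the look is planned at another fraction.

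(b) The primary DFS test uses the FAS, defined as all randomised patients analysed as randomised. PP is supportive and cannot establish the result.

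The cost is a slightly stricter final threshold if an efficacy interim is kept, and the loss of any positive claim from PP alone.

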## Discussion

3

GC is still a major health threat to China, with over half of the world’s incidences occurring in this country (15). The prognosis of GC patients in China is also less optimistic than that of patients in Europe or the US (16). Currently, a multimodal approach comprising surgery, chemotherapy, targeted therapy, and immunotherapy is employed in the management of GC. Among them, surgery is considered the foundation of our strategy in pursuit of complete remission. However, quite a few patients experience recurrence early, even if they undergo curative surgery and adjuvant chemotherapy (17–19). Therefore, the reinforcement of adjuvant immunotherapy for patients with high recurrence probability is necessary.

Adjuvant immunotherapy has been reported to provide clinical benefits. Lee et al. conducted a trial on post-operation hepatocellular cancer patients. The median time of recurrence-free survival was 44.0 months in the immunotherapy group and 30.0 months in the no-adjuvant control group (*P=*0.010) (20). KEYNOTE-716 trial showed that pembrolizumab as adjuvant therapy for up to approximately 1 year for resected stage IIB or IIC melanoma. Compared with placebo, pembrolizumab as adjuvant therapy resulted in a significant reduction in the risk of disease recurrence or death. In the first interim analysis, 54 (11%) of 487 patients in the pembrolizumab group and 82 (17%) of 489 in the placebo group had a first recurrence of disease or died (hazard ratio [HR] 0.65 [95% CI 0.46-0.92]; *P=*0.0066) (21). Thus, adjuvant immunotherapy plays a significant role in improving clinical benefits of patients undergoing postoperative adjuvant treatment.

In ctDNA positive urothelial carcinoma patients, Powles et al. reported an improved DFS and OS in the atezolizumab arm versus the observation arm (22). Therefore, ctDNA positive patients are most probably to benefit from adjuvant immunotherapy. The ATTRACTION-5 study revealed that N+C (Nivolumab plus chemotherapy) vs P+C (placebo plus chemotherapy) in patients with pathological stage III G/GEJ cancer after D2 or more extended gastrectomy did not meet the primary endpoint of RFS. However, benefit of survival was observed in stage IIIc *GC* patients with higher risk of recurrence. The results of these research suggest that post-operation patients that are in increased risk of recurrence, such as later stage and ctDNA positive status, may benefit from reinforcement of immunotherapy.

ctDNA is one of the means to screen out high-risk patients. Postsurgical ctDNA in patients with stage II–IV resectable CRC is found to be associated with higher recurrence risk. In addition, postsurgical ctDNA identified patients with stage II or III CRC who derived benefit from adjuvant chemotherapy (7). In GC, Yang et al. reported a significant correlation of worse DFS/OS and positive ctDNA with a preceded radiographic recurrence by a median of 6 months (9). Thus, we hypothesized that ctDNA sequencing can screen out high-risk post-operation GC patients and reinforce their adjuvant regimen with immunotherapy might yield positive results.

Approximately a number of 10^6^ tumor cells can be detected in ctDNA positive patients (23). While for imaging examination like CT, a number of 10^12^ tumor cells or an 8 mm diameter lesion size can be detected. Thus, ctDNA sequencing can be used to find earlier tumor lesion than imaging examination. Besides, the process of angiogenesis starts as early as the tumor reached the size of 2 mm (24, 25). At the same time, early intervention with antiangiogenics might be more effective.

Prior to this study, we have already conducted two study in advanced GC with similar regimens: SPACE trial (apatinib, camrelizumab and SOX regimen, ChiCTR2000034109) and TALENT trial (Anlotinib, tislelizumab and XELOX regimen, NCT04963088). Both yields promising results. In the SPACE trial, the confirmed ORR was 80.8%, median PFS was 10.2 months (95% CI, 5.5-22.3), with the median OS not reached yet (26). In the TALENT trial, The ORR was 75.86% (95% CI: 57.89%-87.78%), and the DCR was 100% (27). Considering the fact that stage III patients are generally in better condition than those with advanced cancer, we expect this regimen can not only reduce risk of recurrence, but also have tolerable adverse effects. Therefore, it is necessary to reinforce adjuvant immunotherapy and antiangiogenics in ctDNA positive GA/GEJA patients undergoing curative surgery and adjuvant chemotherapy.

Our study aims to explore the potential of ctDNA as a biomarker to screen out the patients that are most at risk for recurrence, and the efficacy and safety of reinforcing adjuvant chemotherapy with targeted as well as immunotherapy in high-risk patients determined by ctDNA status. Both of them are novel to adjuvant treatment of *GC*. This study is also designed to have multiomics analysis, including genomics, transcriptomics, microenvironment immune cell infiltration, radiomics and nutritional analysis, which will help not only to validate the use of ctDNA as an immunotherapy indicator, but also to explore the mechanics that lies beneath. We are the first to report the use of ctDNA as an indicator of reinforced adjuvant therapy, in stage III GA/GEJA. Our data can provide the much needed and long-awaited evidence to support clinical decision in implementing adjuvant immunotherapy in GA/GEJA. However, some limitations remain. Firstly, as a researcher-initiated study, the scale of our study is limited. Expanded trials featuring more patients would provide valuable insight into specific findings derived from subgroups. Secondly, dynamic monitoring of ctDNA status is not applied to all our patients, which means conversion of ctDNA negative patients could be neglected, thus impacts of therapy in this specific population remains unclear. Lastly, only stage III patients, no high-risk stage II patient is enrolled in our study. As early recurrence is also seen in stage II patients, the portion of ctDNA positive patients, prognostic value of ctDNA status and clinical benefit of radical adjuvant therapy cannot be explored in this study. We hope our study can provide novel insights into the clinical use of ctDNA and help to further develop the paradigm of precision medicine.

